### 2.5. Outcome Indicators

For the caregivers, the primary outcome is the proportion of the caregivers who use antibiotics irrationally for their children. If one of the following situations exists, we will define it as irrational drug use: Guardians use antibiotics to prevent colds in children, increase or decrease the dosage of children on their own, reserve antibiotics at home or use residual antibiotics for children. The secondary outcome is scores of caregivers on knowledge, attitude, and behavior of antibiotic use for children. For the school-aged children, the primary outcome is the percentage of each of the questions that are contained in the questionnaires that are answered correctly. The secondary outcome is the scores of each section in the knowledge retention questionnaire.

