
This study will be divided into three phases: pre-intervention, intervention, and post-intervention. In the pre-intervention phase, we will administer the KAP questionnaire and the Knowledge-Retention questionnaire to the caregivers and children to collect baseline data. Baseline data will be collected from June 2018. After baseline data is collected, we will implement health education interventions for the children and guardians, respectively, and it will last for three months. Immediately after the intervention, we will send questionnaires to the studied groups, that is, the children and caregivers. However, for school-aged children, we will again send the Knowledge-Retention questionnaire to them to evaluate the retention of knowledge one month after the intervention. Pre and post-intervention data will be compared between the intervention and the control groups, and we will then analyze the results to assess the impact of the interventions on antibiotics use among children.

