### 2.2. Sample Size

Based on the previous study [40], the rate of irrational use of drugs by guardians for their children is 40% to 70%. Through our educational intervention, we hypothesized a 15% reduction in the rate of irrational drug use among children. We set α = 0.05, 1 − β = 0.9. We used software, Sample Size 2.0, to calculate the sample size, and 231 participants are required for the intervention and control groups. Taking into account the lost population, the invalid questionnaires, and the low response rate, we increased the sample size by 55%, to a total sample size of 720. We will select 180 school-aged students in every school. For each child included in our study, we will also invite their caregiver to participate in the study. In four primary schools, we chose 720 students and 720 caregivers. The sampling process is shown in Figure 1. We also invited teachers to help us to do our study. They are the bridge of communication between researchers and caregivers. Caregivers may not follow the orders from researchers, however most parents will follow tasks that are assigned by the teacher and, therefore, we will invite teachers to help us to implement a smooth intervention. In addition, they will help the researchers to distribute and collect the questionnaires from the children and caregivers. Before the intervention, we will give training to the teachers so that they will know more about our study and will clearly know their duty. In each class, we will invite 1 head teacher to cooperate with us.

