### 2.6. Data Management 

During the period of pre-intervention and post-intervention, we organized the children and their guardians to complete the knowledge retention questionnaire and the KAP questionnaire, respectively, and for the illiterate participants, the researchers will read and explain the content of the questionnaire to them. Two different tools are used in this study: a knowledge retention and KAP questionnaire. Both questionnaires were developed based on published literatures [42,43,44,45,46] and were issued to the children and caregivers in one class before the study. According to the opinion of the children and caregivers, we revised the language of the questionnaire to ensure that the respondents can correctly understand the meaning of each item. In brief, the knowledge retention questionnaire has a total of 26 structured or semi-structured questions which can be divided into five sub sections: (1) Knowledge related to microbes, including differences between bacteria and viruses, and differences between bacterial infections and viral infections. (2) Hand hygiene, including the importance of washing hands frequently, when hands should be washed, and how to wash hands. (3) Respiratory hygiene, including the spread of infectious diseases through coughing or sneezing, and how to prevent the spread of bacteria when sneezing. (4) Food hygiene, including the problems of food contamination and cross-contamination and disposing leftovers and deteriorated foods. (5) Knowledge related to antibiotics, including the basic concepts of antibiotics and indications for antibiotic use, etc. The KAP questionnaire for the caregivers consisted of 30 structured or semi-structured questions, and is divided into four parts: (1) The demographics of the caregivers, including gender, age, educational level, family income, health insurance, and the relationship between the guardians and the children. (2) The knowledge part is to assess the guardian’s cognition of antibiotic-related knowledge, including the relationship between antibiotic use and drug resistance, and the indication of antibiotics. (3) The attitude part includes whether they agree that the use of antibiotics in advance can prevent diseases such as colds, whether children should get antibiotics immediately if they have respiratory tract infections, whether using antibiotics can speed up the recovery of colds and coughs, whether expensive antibiotics are better than cheap ones, and whether caregivers should gain more knowledge about antibiotics, etc. (4) The behavioral part evaluating the behavior of the guardians using antibiotics for their children includes whether they stored antibiotics that were needed by children at home, whether they used antibiotics that were stored at home or the remaining antibiotics, whether they changed the dosage of antibiotics according to the condition of children, and whether they took the initiative to ask doctors to prescribe antibiotics, etc. After the intervention, an evaluation component is added in the KAP questionnaire among the participants in the intervention group, which consists of 12 questions and is intended to evaluate whether the intervention population are satisfied with the intervention measures. Both of the data collection tools were developed after extensive literature searches of related studies and after consulting with experts on infectious diseases in children. All researchers will have a uniform training before the questionnaire is issued to be very familiar with each item in the questionnaire. Once the participants complete the questionnaire, they will be collected by the researchers and will be kept in good condition. We will screen and rule out invalid questionnaires in which the key information is incomplete and is filled out arbitrarily.

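### The children's primary outcome is 26 separate item percentages, with no single primary measure, no labelled primary time point and no rule for a positive result

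*Protocol article*

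**What the plan says.** Section 2.5 (Outcome Indicators) of the protocol article defines the outcomes separately for the two populations. Caregivers have one primary proportion, irrational antibiotic use. For children, "the primary outcome is the percentage of each of the questions that are contained in the questionnaires that are answered correctly". The children's next tier is also plural: "The secondary outcome is the scores of each section in the knowledge retention questionnaire".

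Section 2.6 (Data Management) gives the count: "the knowledge retention questionnaire has a total of 26 structured or semi-structured questions which can be divided into five sub sections". The five cover microbes, hand hygiene, respiratory hygiene, food hygiene and antibiotics.

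Section 2.7 (Data Analysis) repeats that a percentage correct will be computed question by question. It mentions no total score for children and no between-group test of individual items.

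Section 2.1 (Study Design) has children complete the questionnaire at baseline, directly after the three-month intervention, and once more: "we will again send the Knowledge-Retention questionnaire to them to evaluate the retention of knowledge one month after the intervention". It also says that pre- and post-intervention results will be compared between the arms. Neither follow-up is called primary.

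**The concern.** The aim set out in the Introduction concerns a construct, children's knowledge of hygiene and antibiotic use. Twenty-six co-equal percentages cannot give one verdict on that construct, and the article does not say how many items, or which, must improve.

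A mixed pattern is foreseeable from the design itself. Section 2.4 has the children's sessions concentrate on microorganisms, spread and prevention, and makes rational antibiotic use the caregivers' focus. Yet antibiotics form one of the five sections of the children's questionnaire. With no lead measure, the emphasis could settle after the fact on whichever items moved.

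If items are tested one by one without adjustment, some are likely to look significant by chance. At stake is the credibility of the primary result for one of the trial's two participant populations.

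**Working it through.** **The plan's only error-rate figure.** Section 2.2 states "We set α = 0.05, 1 − β = 0.9" and "231 participants are required for the intervention and control groups". I take the midpoint of its 40% to 70% baseline range, 55%, and read the hypothesised 15% reduction as absolute, giving 40%. With a two-sided test and pooled variance under the null:

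n = [1.960·√(2·0.475·0.525) + 1.282·√(0.55·0.45 + 0.40·0.60)]² / 0.15² = (1.384 + 0.895)² / 0.0225 ≈ 231 per group.

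This matches the stated figure, so 0.05 is evidently two-sided. The calculation is for the caregiver proportion. No error rate or power is given for any children's outcome.

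**Inputs for the children's items**
- Number of items: k = 26 (section 2.6).
- Per-item level: 0.05 two-sided, unadjusted. This is an assumption, since the protocol states no item test.
- Correlation between item test statistics: not in the documents. A common value is assumed and varied.
- Each test is taken to hold its nominal level. With two schools per arm that is a separate question, and ignoring clustering would raise every figure below.

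**Independent items, no true effect**
- At least one significant in either direction: 1 − 0.95^26 = 0.736.
- Expected number of false positives: 26 × 0.05 = 1.3.
- At least one significant in favour of the intervention (0.025 per item): 1 − 0.975^26 = 0.482.

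**Correlated items** (simulation of 26 equicorrelated normal test statistics, 200,000 draws per row)

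| Assumed common correlation | Any direction | Favouring the intervention only |
|---|---|---|
| 0 | 0.74 | 0.48 |
| 0.1 | 0.72 | 0.42 |
| 0.2 | 0.68 | 0.37 |
| 0.3 | 0.62 | 0.32 |
| 0.4 | 0.55 | 0.28 |
| 0.5 | 0.47 | 0.24 |

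The any-direction figure crosses 50% between correlations of 0.46 (0.505) and 0.47 (0.498).

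**Alternatives**
- One primary score at one time point: 0.05.
- All 26 items with Bonferroni: 0.05/26 = 0.0019 each, and 1 − (1 − 0.05/26)^26 = 0.049 overall if independent.
- The five section scores promoted unadjusted: 1 − 0.95^5 = 0.226 if independent.

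**The case against.** The strongest reply is that the article never says each item will be tested at 0.05, nor that one significant item is enough. Section 2.7 only promises percentages, and an analysis plan not shown here could adjust for multiplicity. That stands as a limit on the numbers, which are conditional. It does not remove the defect. The outcome definition and hierarchy are fixed in section 2.5, and a correction added elsewhere would still leave 26 primary results without a single answer.

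One might also read section 2.5 as a single overall percentage correct. Its wording refers to each question, and section 2.7 repeats the per-question calculation, so that reading is hard to sustain.

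Three stronger claims are tempting but not supported.
- A reader might infer that a chance positive result is more likely than not. If positive means favouring the intervention, the figure is 48% at most with correctly sized tests. Even counting both directions, the claim fails from a correlation of about 0.47.
- A reader might count two follow-ups as 52 tests and obtain 1 − 0.95^52 = 0.93. That treats the same questions put to the same children a month apart as independent. Section 2.1 also gives the later assessment its own role, retention.
- A reader might say that a single summary number has been demoted to secondary. The secondary outcome is five section scores, and no total is named for children.

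Finally, the only sample-size calculation concerns caregivers' irrational use, a single proportion that this point does not touch. That is fair and bears on severity.

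**Conclusion.** The point holds as a badly fixed outcome definition: 26 co-equal primary items, no single primary measure, no labelled primary time point and no rule for a positive result. This follows directly from the text and needs no assumption.

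The size is conditional. With unadjusted two-sided 0.05 tests that each hold their level, the chance of at least one false-positive item is at most about 74%, and at most about 48% in the favourable direction. Both fall as the items become more correlated, and the documents give no correlation.

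Severity is should-fix. It concerns the children's primary result only.

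**What to change.** In section 2.5, name one primary outcome for children: the total knowledge score (proportion of the 26 questions correct) at the immediate post-intervention questionnaire, adjusted for baseline. Make the one-month total score the secondary outcome for retention, and keep the five section scores secondary. Report the 26 item percentages descriptively with intervals, or Holm-corrected if significance is to be claimed. Simply promoting the five section scores would not be enough, as the 23% above shows.

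A scoring rule for the children's questionnaire has to be added. The one-or-zero rule in section 2.7 is described for the caregivers' KAP questionnaire, and the children's questions include semi-structured ones. Section 2.7 should then be aligned with the new outcome and its baseline adjustment. The choice should be recorded before post-intervention data are seen.

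The cost is a short scoring rule, a few sentences in 2.5 and 2.7, and the loss of unadjusted item-level significance claims. Data collection does not change.

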### 2.6. Data Management 

During the period of pre-intervention and post-intervention, we organized the children and their guardians to complete the knowledge retention questionnaire and the KAP questionnaire, respectively, and for the illiterate participants, the researchers will read and explain the content of the questionnaire to them. Two different tools are used in this study: a knowledge retention and KAP questionnaire. Both questionnaires were developed based on published literatures [42,43,44,45,46] and were issued to the children and caregivers in one class before the study. According to the opinion of the children and caregivers, we revised the language of the questionnaire to ensure that the respondents can correctly understand the meaning of each item. In brief, the knowledge retention questionnaire has a total of 26 structured or semi-structured questions which can be divided into five sub sections: (1) Knowledge related to microbes, including differences between bacteria and viruses, and differences between bacterial infections and viral infections. (2) Hand hygiene, including the importance of washing hands frequently, when hands should be washed, and how to wash hands. (3) Respiratory hygiene, including the spread of infectious diseases through coughing or sneezing, and how to prevent the spread of bacteria when sneezing. (4) Food hygiene, including the problems of food contamination and cross-contamination and disposing leftovers and deteriorated foods. (5) Knowledge related to antibiotics, including the basic concepts of antibiotics and indications for antibiotic use, etc. The KAP questionnaire for the caregivers consisted of 30 structured or semi-structured questions, and is divided into four parts: (1) The demographics of the caregivers, including gender, age, educational level, family income, health insurance, and the relationship between the guardians and the children. (2) The knowledge part is to assess the guardian’s cognition of antibiotic-related knowledge, including the relationship between antibiotic use and drug resistance, and the indication of antibiotics. (3) The attitude part includes whether they agree that the use of antibiotics in advance can prevent diseases such as colds, whether children should get antibiotics immediately if they have respiratory tract infections, whether using antibiotics can speed up the recovery of colds and coughs, whether expensive antibiotics are better than cheap ones, and whether caregivers should gain more knowledge about antibiotics, etc. (4) The behavioral part evaluating the behavior of the guardians using antibiotics for their children includes whether they stored antibiotics that were needed by children at home, whether they used antibiotics that were stored at home or the remaining antibiotics, whether they changed the dosage of antibiotics according to the condition of children, and whether they took the initiative to ask doctors to prescribe antibiotics, etc. After the intervention, an evaluation component is added in the KAP questionnaire among the participants in the intervention group, which consists of 12 questions and is intended to evaluate whether the intervention population are satisfied with the intervention measures. Both of the data collection tools were developed after extensive literature searches of related studies and after consulting with experts on infectious diseases in children. All researchers will have a uniform training before the questionnaire is issued to be very familiar with each item in the questionnaire. Once the participants complete the questionnaire, they will be collected by the researchers and will be kept in good condition. We will screen and rule out invalid questionnaires in which the key information is incomplete and is filled out arbitrarily.

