## 2. Materials and Methods

### 2.1. Study Design

We will conduct a multistage cluster randomized controlled trial at the school-level. Our study will be carried out in primary schools in the Shaanxi Province, western China. According to the economic level of the Shaanxi Province, two clusters were formed: developed areas, where we chose Baoji, and Weinan from the less developed areas. The chosen primary schools from both of the study sites met the following inclusion criteria: (1) Schools must be willing to take part in our study; (2) Schools should be in urban areas with enough teachers and students. In rural areas, most young people need to go out to work and earn a living, leaving the elderly to look after the children. Socio-demographic characteristics are quite different between rural and urban areas, so we only include urban primary schools. (3) Schools are theoretically matched and are comparable with each other in terms of school size and teaching level; (4) Must be public primary schools because private primary schools are mainly composed of students with higher family incomes. (5) Two schools in each city must be in different districts or in different streets. The distance between the two schools in each city must be more than 5 km. Based on the inclusion criteria and the referenced CONSORT (Consolidated Standards of Reporting Trials) statement for randomized trials [39], a final selection of two primary schools in each city will be made. In total, there are 804 public primary schools in Baoji and 638 public primary schools in Weinan. Among these schools, in Baoji there are 37 schools in urban areas and 767 in county or in rural areas. For the schools in urban areas, 10 schools are unwilling to participate in our study and 17 schools are small scale (which have less than three classes in the fifth grade or less than 1500 students in schools). Taking the distance between the two schools in the same city into account, we chose two schools from the remaining 10 schools. In Weinan, there are 23 schools in urban areas and 615 in counties or in rural areas. The sampling process was similar in Weinan and we have depicted it in Figure 1 (The sampling process). In each city, one primary school will be randomly selected for the intervention group and the other will serve as the control group. The study participants will be chosen from the class level and in every school we will select three to five classes from the fifth grade at random. Participants will be selected based on the inclusion criteria from the chosen classes and they will be blinded on their assigned group.

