### 2.4. Intervention Procedures

The purpose of the intervention is to change the knowledge, attitude, and behavior of guardians about the use of antibiotics for children with upper respiratory tract infections and, at the same time, to improve children’s knowledge about antibiotics use and to help them build awareness of preventing infection. We have created a WeChat (the most popular web-based social media tool in China) official account, through which we will push educational materials about the rational use of antibiotics to guardians. Only participants in the intervention group will have access to the information in the WeChat platform. Besides, participants are required to not share the information to others during the intervention period. For those caregivers who do not have WeChat accounts, we will distribute paper education materials separately, which will be the same as the electronic one. The educational materials are from the Center for Disease Control and Prevention in America [41]. Under the circumstance of China, we will translate the educational materials into Chinese and will make them easy to understand. We developed booklets about rational antibiotics use in children which cover the basic concept of antibiotics, antibiotic resistance, bacterial and viral infections, indications of antibiotics, and problems that can be encountered with the use of antibiotics and so on. The booklets will be taken home by the students. Both the students and the caregivers are required to study the booklet with commands from the teachers. Additionally, every month within a 3-month period, experts in the field will conduct a 1.5-h interactive training session for the children and their caregivers, and before each training session, we will issue them with the teaching materials. The content of the training session mainly includes four aspects: knowledge on microorganisms, the spread of infection, the prevention of infection, and the rational use of antibiotics for respiratory diseases. However, the training session for the caregivers will focus on the rational use of antibiotics and that for the children will concentrate on the knowledge of microorganisms, the spread of infection, and the prevention of infection. In the control group, both the children and caregivers will have no access to any intervention measures.

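### Staff who can infer the arm are told to explain the outcome questionnaires to illiterate participants, which leaves room for arm-dependent prompting; the effect is probably small and cheap to prevent

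*Protocol article*

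**What the plan says.** Section 2.6 (Data Management) describes how the questionnaires are given: "During the period of pre-intervention and post-intervention, we organized the children and their guardians to complete" the two instruments, and "for the illiterate participants, the researchers will read and explain the content of the questionnaire to them". So the help is offered at both waves. The safeguard described is uniform training that makes researchers familiar with every item. Section 2.6 mentions no script for reading aloud.

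On blinding, section 2.1 says of the participants that "they will be blinded on their assigned group". It does not mention the researchers who administer the forms. Section 2.1 allocates whole schools, one to each arm in each city. Section 2.4 adds: "In the control group, both the children and caregivers will have no access to any intervention measures". After the intervention, according to section 2.6, "an evaluation component is added in the KAP questionnaire among the participants in the intervention group"; it has 12 questions.

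On format, "the knowledge retention questionnaire has a total of 26 structured or semi-structured questions" and "The KAP questionnaire for the caregivers consisted of 30 structured or semi-structured questions". Section 2.7 gives the caregivers' knowledge items three closed options scored 1 or 0, and puts attitude and behaviour on a Likert scale. For the children, section 2.5 says that "the primary outcome is the percentage of each of the questions that are contained in the questionnaires that are answered correctly".

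**The concern.** A knowledge item measures what the respondent knows, and explaining its content can supply the answer. A behaviour item measures what the caregiver reports doing, and explaining it can signal which reply is wanted. If the person explaining knows or can guess the arm, the amount and tone of help may differ between arms without anyone intending it.

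The caregiver primary outcome is directly exposed. Section 2.5 defines it by four behaviours. Three of them (changing the dose, keeping antibiotics at home, using leftover antibiotics) match behaviour items listed in section 2.6.

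A bias of this kind follows the allocation. With two schools per arm, analysis cannot separate it from the intervention effect, and enrolling more pupils does not reduce it.

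**Working it through.** **1. The yardstick: the planned difference.** Section 2.2 gives a rate of irrational use of 40% to 70%, a reduction of 15%, α = 0.05, power 0.90 and 231 participants. Take the reduction as percentage points, two-sided α, pooled variance and no continuity correction:

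n per group = [1.960·√(2·p̄·(1−p̄)) + 1.282·√(p₁(1−p₁) + p₂(1−p₂))]² / (p₁−p₂)²

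With p₁ = 0.55, p₂ = 0.40 and p̄ = 0.475:
- 1.960 × √0.49875 = 1.384
- 1.282 × √0.4875 = 0.895
- (1.384 + 0.895)² / 0.0225 ≈ 231

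The pair 0.60 and 0.45 also gives 231. A relative reduction of 15% would need 770 per group at 0.55, and 433 to 1,359 over the stated range. So the plan's figure reproduces as 231 per group, and the planned effect is 15 percentage points. Then 2 × 231 × 1.55 = 716, close to the stated 720, or 360 per arm.

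**2. Can the person explaining tell the arm?** The article does not say so in words. Three stated facts make it easy:
- The arm is a property of the school.
- Control schools receive nothing.
- After the intervention, the caregiver form carries the 12 extra questions only in the intervention group.

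**3. Which outcomes are exposed?** Help goes only to illiterate participants. The children are fifth graders in urban public schools, so few should need it. Caregivers are the more likely recipients.

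**4. Size of the bias.** The article does not give the share assisted, so these inputs are assumptions:

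bias = (share assisted) × (shift in their answers, in one arm only)

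| Share assisted | Shift of 10 points | Shift of 30 points |
|---|---|---|
| 1% | 0.1 | 0.3 |
| 5% | 0.5 | 1.5 |
| 10% | 1.0 | 3.0 |
| 20% | 2.0 | 6.0 |

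Entries are percentage points on the caregiver primary outcome, to be read against 15.

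**5. Effect on a null comparison.** Assume no true effect, a rate of 0.55, 360 per arm and no clustering. For a bias b:

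SE = √(0.55·0.45/360 + (0.55−b)(0.45+b)/360)

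rejection probability = Φ(b/SE − 1.96) + Φ(−b/SE − 1.96)

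With b = 0.015, SE = 0.0371 and b/SE = 0.404, so the probability is Φ(−1.556) + Φ(−2.364) = 0.069. Over shares of 1% to 5%, the nominal 5% error becomes about 5.0% to 6.9%. Over shares of 10% to 20%, it becomes 5.8% to 36%; the top figure needs a 20% share and a 30-point shift together.

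**The case against.** The strongest reply is that explaining may mean no more than clarifying the wording. Section 2.6 says that the language was revised after a trial in one class so that respondents understand each item, and that all researchers are trained alike. The procedure is stated for all illiterate participants at both waves, without distinction by arm, and equal prompting in both arms does not produce the bias described here. This stands in part: differential prompting is a possibility that the procedure allows, not something that the article describes. But training for familiarity with the items is not training for neutrality, and nothing quoted limits the explanation to wording.

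The reply that few people will be assisted also stands. These are urban schools, and section 2.3 requires caregivers with normal understanding and communication skills. That limits the size of the bias, above all for the children's primary outcome.

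A reader might go further and infer that staff must judge the answers to semi-structured questions, so that lenient marking by arm could enter the scores. The article does not support this. The scored caregiver sections are closed or on a Likert scale. For the children's questionnaire no response format or marking rule is given, so judgement is at most possible there. An answer key is detail that a condensed article commonly leaves to a fuller document, and its absence is not a fault. A reader might also take it as stated that the researchers know the arm; that is a strong inference, not plan text.

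**Conclusion.** The point holds in a limited form. A stated procedure lets staff who can readily infer the arm explain outcome items freely, and no blinding of these staff is stated. The exposure lies mainly in the caregiver outcomes.

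On the assumption that 1% to 5% are assisted, with a shift of 10 to 30 points in one arm, the bias is 0.1 to 1.5 points against the planned 15. Larger values, up to 6 points, need an assisted share of 10% to 20%, which seems unlikely in this population but which the article does not rule out. The direction is also not fixed by the text; the calculation takes the direction that favours the intervention.

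This is a cheap improvement to make, not a threat to the trial's main conclusion.

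**What to change.** 1. In section 2.6, replace the instruction to read and explain with this: read each item and its options aloud, word for word, from one script used in both arms, without explaining content. Cover this in the researcher training already planned.
2. Flag every assisted questionnaire and add a sensitivity analysis that leaves these questionnaires out in both arms.
3. Hand out the 12 satisfaction questions as a separate sheet after the caregiver form has been collected, so that the outcome form itself does not reveal the arm. The school will still suggest it, which is why the script matters most.
4. If any of the children's items take open answers, have existing staff mark them from sheets that show only the identification number already planned in section 2.8, with schools mixed.

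Cost: no extra staff or visits. Expect slightly more don't-know answers from participants who cannot read, and minor work in handling and shuffling sheets.
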